### Randomization

Researchers plan for hospital-based randomization in both study centers from 1
^st^ December 2022 to 30
^th^ May 2023 by sequential random sampling and eligibility screening. Participants were randomly assigned to either the therapeutic exercise plus education booklet (TEB) group or the therapeutic exercise plus vitamin D3 supplementation (TED) group using a computer-generated randomization sequence. Randomization was stratified by study center to ensure balanced distribution across sites. Allocation concealment was maintained through the use of sequentially numbered, opaque, sealed envelopes prepared by an independent researcher not involved in recruitment or assessment.

Blinding was implemented at multiple levels to minimize bias. Outcome assessors were blinded to group allocation throughout the study, ensuring objective evaluation of pain, disability, and serum vitamin D levels. Data analysts were also blinded to group identity during statistical analysis. Due to the nature of the interventions, participants and treating physiotherapists could not be blinded; however, strict separation between intervention delivery and outcome assessment was maintained to preserve methodological rigor.

### Recruitment and study procedure

We will follow the Consolidated Standards of Reporting Trials (CONSORT) to maintain the standards of the study procedure (
Figure 1). For the initial recruitment the LBP patients attending outdoor clinics of both centers from 1st December 2022 to 30th May 2022 will be primarily screened by the outdoor team and provided participant information sheet (PIS) of the study. The final screening will be performed by two licensed physician specializing in physical medicine and rehabilitation. These physicians held postgraduate qualifications (MD/MS in Rehabilitation Medicine or Orthopedics) and had a minimum of 5–10 years of clinical experience in musculoskeletal disorders and pain management. The patient will meet the blinded assessor who will then take pretest data in a separate room, and collect a blood sample, before returning the patient to the outdoor pool. From outdoor pool, the patient will have a concealed envelop with another random ID number matched by the initial ID number given and meet the intervention provider (physiotherapist and physician or physiotherapist alone). Patient will receive the intervention provided in the written guideline enclosed in the concealed envelope. After 8 weeks of treatment completion, the patient will be further screened by blinded assessor, and another blood sample will be collected before discharge. After six months, the patient will be invited to the treatment center or visited in their house or workplace for follow up evaluation and blood sample collection. Therapeutic exercise will be provided by a graduate physiotherapist, and medication will be provided by a registered medical practitioner. Patient will pay for the physiotherapy treatment sessions but will not pay for any additional blood tests, medication or booklet.

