Chronic low back pain (CLBP) has been associated with vitamin D deficiency, which affects calcium metabolism, bone health, and muscle function. Deficiency may lead to osteomalacia, muscle weakness, and impaired neuromuscular control, increasing spinal instability and pain. Additionally, low vitamin D levels can elevate pro-inflammatory cytokines, intensifying pain sensitivity and contributing to chronic musculoskeletal disorders.
^
8
^ Clinical studies have reported a higher prevalence of vitamin D deficiency among patients with CLBP compared to healthy controls, suggesting a potential association between deficiency and pain severity.
^
17,
18
^ Vitamin D supplementation has been explored as a supportive measure in CLBP due to its role in bone health, muscle strength, and inflammation regulation.
^
19
^ Correcting deficiency may improve musculoskeletal function and reduce pain sensitivity, with clinical trials reporting symptomatic improvement in deficient patients.
^
20,
21
^ However, meta-analyses indicate limited overall efficacy, suggesting benefits may be restricted to those with confirmed deficiency, while excessive intake carries risks such as hypercalcemia and kidney stones.
^
22
^

This study hypothesizes that multidimensional comprehensive management through therapeutic exercise combined with an education booklet on sun exposure, nutrition, and lifestyle (TEB) will be superior to therapeutic exercise with oral vitamin D supplementation (TED) in patients with chronic low back pain and vitamin D deficiency. Specifically, it is expected that participants in the TEB group will demonstrate greater improvements in pain symptoms, serum vitamin D levels, and disability status compared to those in the TED group, with these effects observed at both 2 and 6 months following baseline recruitment. Following the study hypothesis, this trial holds clear clinical significance: for clinicians, it offers evidence to guide treatment choices between exercise combined with education or vitamin D3; for patients, it evaluates accessible, low-cost strategies that may improve pain and function; and for researchers, it provides rigorous comparative data to inform future studies on scalable interventions for CLBP.

The specific objectives are:

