## Methods

Researchers plan for an assessor blinded two arm multicenter Randomized Clinical Trial (RCT) protocol to compare the efficacy of therapeutic exercise and an education booklet on sun exposure, nutrition and lifestyle versus therapeutic exercise and oral vitamin D supplement for CLBP patients with vitamin D deficiency at 2 months and 6 months after baseline recruitment in designated rehabilitation centers in Dhaka city.

For this potential trial, researchers will follow Standard Protocol Items: Interventional Trials 2013 (SPIRIT) guidelines, to help ensure quality of the interventional trial (
Table 1).

**Table 1. T1:** Study protocols according to SPIRIT guidelines.

Study (Status)	Teams (Preparation)			Patients (Execution)			
	Preparation & planning	Training to team	Piloting	Enroll	Study		
Time					Baseline 0	2 months	6 months
**Intervention**	×	×	×		×	×	
**Enrollment**	×		×	×			
Informed Consent	×		×	×			
Eligibility	×	×		×			

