### Eligibility criteria

Participants will be included if they present with chronic low back pain (CLBP) of central origin, persisting for more than three months and classified under ICD-10-CM Code M54.5, with documented vitamin D deficiency defined as serum 25(OH)D3 levels below 20 ng/mL.
^
16
^ Eligible individuals must be adults aged 18 years or older, of either gender, residing or working in Dhaka city in office, industry, or corporate settings that involve static postures or desk jobs requiring at least six hours of sitting per day for an average of 22 days per month, and must provide informed consent. Exclusion criteria comprise comorbid conditions that may influence vitamin D metabolism or bone health, including rheumatoid arthritis, ankylosing spondylitis, osteomalacia, tuberculosis of the spine, or a history of osteoporotic fracture. Women over 50 years of age or those who are post-menopausal will also be excluded,
^
14
^ as will individuals with prior use of calcium or vitamin D3 supplements, resistance training, or high-impact weight-bearing activities within the past six months. Patients presenting with neurological red flags such as dural signs, positive straight leg raise test, or bowel/bladder incontinence will not be considered. Additional exclusions include current participation in another clinical study and withdrawal during the 8-week intervention period.

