We expect there will be no major adverse effect for therapeutic exercise and booklet group and that there will be no request of dosage change or worsening of patients’ condition. If any of these occur we will discuss with the patient. If the patient is not willing not to continue, we will stop the intervention, and keep the data for intention to treat analysis. The vitamin D supplement group may experience some adverse effect; we will manage as per the standard measures described in the “safety measures” section. The adherence to these interventions will be monitored through checklist (Extended data 1
^
37
^). We will also monitor adverse effect using a checklist (Extended data 2
^
37
^).

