## Discussion

There is an increasing concern of LBP and vitamin D deficiency for chronic pain suffers that is leading the working people towards disability and inefficiency to work.
^
5
^
^,^
^
9
^ A non-randomized quasi experimental study
^
10
^ found therapeutic exercise and vitamin D oral supplementation is effective to reduce pain, replenish vitamin D3 level with short term results. Our study will meet the necessity of randomized systematic evaluation of therapeutic exercises and vitamin D supplement compensation in two different approaches, either by sun exposure, nutrition and healthy lifestyle or by taking oral supplements. We will evaluate outcome in both short term (2 months) and long-term effect after 6 months of stopping the intervention. The experimental group is the therapeutic exercise and booklet group because we assume a positive lifestyle and exercise can replace the role of oral medication supplement, as these were derived as a predictor in observational studies.
^
9
^

The methodological standard of the proposed trial adheres to the Enhancing the QUAlity and Transparency Of health Research (EQUATOR) guidelines to ensure the rigor of the study. As this is a two tailed hypothesis, we assume any treatment can be superior or both may have similar effect. The similar effect is also a positive finding, because oral vitamin D supplement have some adverse effects if taken for longer durations.
^
12
^ Moreover, if the study would have four arms including two interventions, a group with only vitamin D supplement and another with therapeutic exercise and a placebo vitamin D supplement, that could ensure true effects. However, researchers had to limit the study considering funding, scope of practice and complicated management issues. As outcome indicators pain and vitamin D3 levels will be used as primary outcomes and disability as secondary outcome, because previous research suggests disability as a consequence.
^
36
^ BPI measures not only pain severity, but also pain affective interference and pain physical interference,
^
10
^
^,^
^
30
^ that is consistent to the effect of intervention.

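### The visit anchors conflict, and followed literally the procedure text can leave patients who stop treatment early without 2-month outcomes

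*Protocol article*

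**What the plan says.** **Second assessment.** Recruitment and study procedure is the only place that describes how this visit is carried out: "After 8 weeks of treatment completion, the patient will be further screened by blinded assessor, and another blood sample will be collected before discharge". The opening of Methods compares the arms "at 2 months and 6 months after baseline recruitment". The hypothesis in the Introduction agrees: "with these effects observed at both 2 and 6 months following baseline recruitment". Table 1 marks BPI, vitamin D and RMDQ at baseline, 2 months and 6 months, with no condition attached.

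**Long-term assessment.** The procedure text places it after six months without saying from when, and adds a tracing route: "the patient will be invited to the treatment center or visited in their house or workplace for follow up evaluation". The Discussion describes it as the "long-term effect after 6 months of stopping the intervention".

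**Patients who stop.** For a patient who does not continue, Interventions says: "we will stop the intervention, and keep the data for intention to treat analysis". Eligibility criteria, on the other hand, state: "Additional exclusions include current participation in another clinical study and withdrawal during the 8-week intervention period". The Abstract and Data analysis both commit to intention to treat, and Data analysis relies on that principle to handle missing data.

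**The concern.** Pain and serum 25(OH)D are both primary outcomes, and 2 months is a hypothesised time point for each. If the visit is tied to completing treatment and being discharged, a site has no instruction for a patient who stops in week 3, because that patient reaches neither event. Keeping such a patient's data does not tell anyone to collect more. Listing withdrawal as an exclusion suggests that the patient is out of the trial.

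The 2-month comparison could then rest mainly on completers while being reported as intention to treat. No later analysis plan can supply measurements that were never taken. Stopping is plausible: the schedule is four sessions a week for 8 weeks, patients pay for their sessions, and they know their allocation. The arms also differ in capsules and physician contact, so stopping need not be balanced between them.

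**Working it through.** **1. The anchors side by side**

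| Place in the protocol | Second assessment | Long-term assessment |
|---|---|---|
| Introduction (hypothesis), Methods (opening) | 2 months from baseline | 6 months from baseline |
| Table 1 | 2 months, all patients | 6 months, all patients |
| Recruitment and study procedure | at treatment completion, before discharge | after six months, start not stated |
| Discussion | short term, 2 months | 6 months after treatment stops |

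For a patient who completes 8 weeks on schedule, the first three rows agree on the second assessment to within days. They part for a patient who stops early. The baseline anchor still yields a 2-month visit. The completion anchor yields none.

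The long-term anchors differ even for completers. Eight weeks is 56/30.4 = 1.8 months, so six months after stopping is 1.8 + 6 = 7.8 months from baseline. For a patient who stops at 3 weeks it is 21/30.4 + 6 = 6.7 months. Under the Discussion's wording the visit would therefore move with treatment duration.

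**2. What happens to a patient who stops**

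- Interventions: treatment stops and the data are kept. Further assessment is neither promised nor ruled out.
- Eligibility criteria: withdrawal in the 8 weeks is an exclusion. It can only occur after enrolment, so it conflicts with intention to treat.
- Recruitment and study procedure: home or workplace tracing is described for the long-term visit only. That visit is not conditional on completion.

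The outcome set at risk is therefore the 2-month one.

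**3. Possible bias (illustration)**

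The protocol gives no stopping rates and no outcomes for stoppers, so every input here is assumed. Let pA and pB be the stopping proportions, and let δ be the amount by which stoppers improve less than completers, the same in both arms. A completers-only contrast differs from the all-randomised contrast by (pA − pB) × δ.

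- 20% v 10%, δ = 1.5 BPI points: 0.10 × 1.5 = 0.15 points.
- 30% v 10%, δ = 3 BPI points: 0.20 × 3 = 0.6 points.
- A 10-point difference with δ = 0.3 to 0.8 SD: 0.03 to 0.08 SD.

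If stopping is equal in the arms, this term is zero.

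**4. Possible loss of power (illustration)**

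Sample size cites a minimum of 152 at α = 0.05 and 80% power, with no effect size or SD, so the figure cannot be reproduced, only inverted. Taking 152 as the total, 76 per arm and two-sided α: d = (1.960 + 0.842) × √(2/76) = 0.454.

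| Assumed share without a 2-month outcome | Power with 152 randomised | Randomised to keep 152 evaluable |
|---|---|---|
| 5% | 78% | 160 |
| 10% | 76% | 169 |
| 20% | 71% | 190 |
| 30% | 65% | 218 |

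The right-hand column is 152/(1 − share), rounded up. The protocol plans extra recruitment for attrition but does not say how much.

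**The case against.** The strongest reply is that this is one loosely worded sentence against a clear schedule. Treatment is defined by duration, so the end of 8 weeks of treatment is simply about 2 months. Table 1 schedules the visit for everyone, and several sections name 2 months. The article is condensed, it points to a registered protocol, and its participant-flow figure is not shown. Silence on follow-up after stopping may be filled there.

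Much of this stands, and it rules out several stronger readings that a reader might infer:

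- *That 2-month visits will run late.* Four sessions a week for 8 weeks is 32 sessions. If all had to be attended, a patient coming three times a week would finish at 32/3 = 10.7 weeks, and one coming twice a week at 32/2 = 16 weeks. The protocol states no session quota and no make-up of missed sessions, so these delays, and any dilution of the supplement arm from late blood samples, are not supported.
- *That only data already in hand are kept.* The sentence does not say so. This is an inference from silence.
- *That nothing is collected after stopping.* The 6-month visit is not tied to completion.
- *That the keep-the-data rule covers the booklet arm only.* The sentence follows an expectation about that arm, but the text does not clearly confine it there, and intention to treat is stated for the whole analysis.
- *That patients who want to continue would be stopped.* The double negative in the stopping sentence is a language slip.

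The reply does not remove the conflict. The text that staff would follow uses treatment completion and discharge, the Discussion uses a further anchor, and the withdrawal exclusion points towards dropping stoppers. These are things the article states, not details it leaves elsewhere.

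**Conclusion.** The concern holds as a conflict between stated visit anchors, made more serious by the stopping and withdrawal wording. Followed literally, the procedure text can leave patients who stop early without 2-month BPI, RMDQ and 25(OH)D, contrary to the protocol's own intention-to-treat commitment. This is a possible consequence of the wording, not a declared intention, and it concerns the 2-month visit.

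Its size cannot be taken from the document. The bias and power figures in the working depend on assumed stopping rates and outcome gaps, and the direction of any bias is unknown. The change should be made because it protects both primary outcomes at a hypothesised time point at almost no cost.

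**What to change.** 1. **Recruitment and study procedure:** anchor both assessments to the date of allocation or baseline, with a fixed window (for example 8 weeks plus or minus 1 week for the second), regardless of sessions attended or capsules taken. Remove completion and discharge as triggers.
2. **Discussion:** describe the long-term visit from the same anchor.
3. **Interventions:** state one rule for both arms. Stopping treatment is not leaving the study, and BPI, RMDQ and 25(OH)D are still collected at 2 and 6 months unless the patient withdraws consent to follow-up.
4. **Eligibility criteria:** reconcile the withdrawal exclusion with that rule and with intention to treat.
5. **Tracing:** allow the home or workplace visit already planned at 6 months to be used at 2 months for patients who no longer attend.

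The sponsor must also reconcile the wording on when treatment is stopped; no clinical rule is proposed here.

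The cost is a few sentences and a small number of extra visits, using a procedure the trial already has.

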**Figure 1. f1:**
[figure not shown]
CONSORT diagram.

### Monitoring

Patients will be monitored during the intervention session, and the medication chart and home exercise checklist (Extended data 1
^
37
^) will be maintained for recording the interventions. Patient data will be reviewed by a team from a different organization out of the study setting. The completed forms and questionnaire, along with blood report, will be evaluated by the monitoring team. Any kind of change or modifications to the methodology and intervention protocol will be communicated to the Ethics Committees. The research team will have access to the data and interim results and be in charge of making the final decision to change or end the study, hence carrying out interim analysis.

### Safety measures to avoid harmful effects

Although it is expected that vitamin D3 supplementation and therapeutic exercise will not produce harmful effects on patients, patients should be instructed to inform the physician and physiotherapist if they feel any kind of discomfort (including-gastrointestinal, skin, musculoskeletal problem etc.) after the intervention. Before starting, the physiotherapist and physician will screen patients for any contraindications to intervention. If any serious harmful effects are found, researchers will report this during the final publication. The adverse effects reporting checklist will be provided during intervention (Extended data 2
^
37
^).

### Data analysis

Data will be analyzed based on its nature. Calculation and data auditing will be done using Microsoft Excel 2016. Data will be analyzed by SPSS version 23, and R-4.2.1 for Windows. Eligibility for parametric analysis will be checked using bell’s curve, skewness, kurtosis, Kolmogorov–Smirnov test and Shapiro–Wilk test. Continuous variables will be represented by using an arithmetic mean and standard deviation. Categorical data will be represented by percentage (%) and frequency. Baseline characteristics between groups will be compared using chi-square tests for categorical variables and independent t-tests or Mann–Whitney U tests for continuous variables, depending on data distribution. Normality will be assessed using the Shapiro–Wilk test. For within-group comparisons across time points (baseline, 2 months, and 6 months), repeated measures ANOVA will be applied for parametric data, with Greenhouse–Geisser correction if sphericity is violated; the Friedman test will be used for non-parametric data. Between-group differences over time will be analyzed using mixed-model repeated measures ANOVA, which accounts for group × time interactions, or generalized estimating equations (GEE) if assumptions are not met. Post-hoc pairwise comparisons will be adjusted using Bonferroni correction. Effect sizes (Cohen’s d or partial eta squared) will be reported to indicate the magnitude of differences. All analyses will be conducted at a two-tailed alpha level of 0.05, and intention-to-treat principles will be applied to handle missing data.

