**Booklet contents (B):**
^
24–
26
^

The educational booklet provides lifestyle and self-management advice designed to complement therapeutic exercise. Key recommendations include:
•Avoid prolonged static sitting or standing; alternate between sitting and standing during work.•Consume natural sources of vitamin D3 such as milk, yogurt, fortified cereals, orange juice, mushrooms, margarine, hard-boiled eggs, and sea fish (e.g., tuna, salmon).•Engage in 30–35 minutes of sun exposure between 11:00 am and 2:00 pm.•Maintain 7–8 hours of sleep per night.•Avoid stress, smoking, and alcohol consumption, while maintaining a healthy body weight.•Perform regular physical activity as part of daily routine.

Therapeutic exercise protocol (TE):
^
27–
29
^

Both groups will receive therapeutic exercises. Exercises will focus on both back pain and disability minimization of the participants. Each session will last for 25-30 minutes, 4 days per weeks and for 8 weeks. The progression of therapeutic exercise will be as per the registered protocol. Exercises are delivered under a physiotherapist supervision and include:
•Postural advice (TH.1): Maintain erect posture in sitting and standing; avoid prolonged sitting/standing and forward bending.•McKenzie’s directional preference exercises (TH.2): Sustained positioning and repeated movements, most often extension-based, performed in sets of 10 repetitions.•Stretching exercises (TH.3): Targeting erector spinae, hamstrings, and triceps surae muscles.•Lumbar stabilization exercises (TH.4): Core strengthening to enhance spinal stability.•Weight-bearing aerobic exercises (TH.5): Jogging, stair climbing, and 30 minutes of brisk walking.•Heating modalities (TH.6): Infra-red radiation applied as adjunct therapy.

Vitamin D supplementation (D):

Participants in the TED group will receive 40,000 IU vitamin D3 capsules once weekly for 8 weeks, prescribed by a registered physician and manufactured by a licensed pharmaceutical company in Bangladesh.
^
23
^

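### Within-arm change in 25(OH)D is read as effectiveness, but enrolment from December to May puts baseline and 6-month samples in different seasons

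*Protocol article*

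**What the plan says.** **Enrolment.** The Randomization section places it in a single half-year: "Researchers plan for hospital-based randomization in both study centers from 1" December 2022 to 30 "May 2023 by sequential random sampling and eligibility screening". The Recruitment and study procedure section gives the same months with an end year that precedes the start ("from 1st December 2022 to 30th May 2022 will be primarily screened"). I read that year as 2023.

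**Follow-up clock.** The Methods opening sets the assessments "at 2 months and 6 months after baseline recruitment in designated rehabilitation centers", and the hypothesis in the Introduction does the same. The Discussion instead places the long-term assessment six months after the intervention ends. The Recruitment section does not say when its six months start.

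**Outcome and sunshine.** Serum 25(OH)D is one of two primary outcomes. The Introduction associates low sunshine exposure in city dwellers with insufficient vitamin D. The booklet given to the experimental arm advises: "Engage in 30–35 minutes of sun exposure between 11:00 am and 2:00 pm".

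**Analysis.** Objectives 2 and 3 assess each arm separately against its own baseline; objective 4 compares the arms. The within-arm test is fixed: "For within-group comparisons across time points (baseline, 2 months, and 6 months), repeated measures ANOVA will be applied for parametric data", with Friedman as the non-parametric alternative. For the comparison of arms: "Between-group differences over time will be analyzed using mixed-model repeated measures ANOVA, which accounts for group × time interactions", or GEE if assumptions fail. Season is not mentioned anywhere.

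**The concern.** If all baselines come from one half of the year and all 6-month samples from the other, a within-arm test of visit cannot tell treatment from season. The plan nevertheless presents that test as evidence of effectiveness in each arm.

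Two statements in the Discussion raise the stakes. It says that similar results in the two arms would also be a favourable finding, and it concedes that the additional arms needed to isolate true effects were not feasible. Both arms moving together with no difference between them is exactly the pattern that season alone could produce. The Discussion also expects insight into how exercise affects vitamin D metabolism. Both arms exercise, so that inference can rest only on the time trend.

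**Working it through.** The plan has no figure of its own on season, so there is none to reproduce.

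**Step 1: dates.** The inputs are the enrolment window (Randomization, 181 days), the two clocks, and the 8-week course (Interventions).

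| Visit | Counted from | Sampling window |
|---|---|---|
| Baseline | – | 1 Dec 2022 to 30 May 2023 |
| 2 months | baseline | 1 Feb to 30 Jul 2023 |
| 6 months | baseline | 1 Jun to 30 Nov 2023 |
| Last visit | end of 8-week course, plus 6 months | 26 Jul 2023 to 25 Jan 2024 |

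On the baseline clock, the baseline and 6-month windows share no calendar month. On the Discussion's clock, 55 of the 181 entry dates (30%) lead to a last sample in December or January; the rest fall in July to November.

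**Step 2: season-only change within an arm.** Assumptions, not in the documents: entry is uniform over the window, and 25(OH)D follows an annual cosine of amplitude A (trough-to-peak swing 2A) that peaks on day p, counted from 1 January. The window is centred on about day 59. A six-month lag reverses the cosine, and averaging over about half a year multiplies it by about 2/π, so

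mean change ≈ −(4/π) · A · cos[2π(59 − p)/365.25], with extremes ±(4/π)A = ±1.27A.

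Averaging day by day gives:

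| Peak day p | 6 months from baseline | 6 months after stopping |
|---|---|---|
| 120 | −0.63A | −0.95A |
| 150 | about 0 | −0.53A |
| 180 | +0.62A | +0.03A |
| 210 | +1.09A | +0.58A |
| 240 | +1.27A | +0.98A |

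Over all peak dates the ranges are −1.27A to +1.27A and −1.13A to +1.13A.

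**Step 3: what the tests would do with no treatment effect.** This was simulated with 76 per arm (the stated minimum of 152, read as a total), assumed between-person SD 3.5 and within-person SD 2.5 ng/mL, and 2,000 runs per setting. The tests were a one-sample t-test of the baseline-clock 6-month change within one arm and a two-sample t-test of change between arms, both at 0.05.

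| A (ng/mL) | Within-arm rejection, p = 180 to 240 |
|---|---|
| 0 | about 5% |
| 1 | 30% to 87% |
| 2 | 72% to 100% |

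The between-arm test rejected in 4% to 6% of runs in every setting, with bias about zero. These peak dates all give a rise; for p near 150 the mean shift vanishes.

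**Step 4: when could the between-arm contrast be affected?** With uniform entry over 181 days, the SD of entry date is 181/√12 = 52 days. With 76 per arm, the standard error of the between-arm difference in mean entry date is 52 × √(2/76) = 8.5 days. A one-month gap (30.4 days) is therefore about 3.6 standard errors, and randomisation within centre makes it very unlikely. It becomes plausible only if each arm has its own site and the sites recruit on different calendars. As an example, let one arm enter over the first 121 days and the other over the last 121, so that mean entry differs by 60 days. The contrast then shifts by 1.42A, 0.84A and 0.04A for peaks at days 180, 210 and 240.

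**The case against.** **The trial is comparative.** The hypothesis, the stated aim and objective 4 all concern the difference between arms. With concurrent randomisation stratified by centre, season is common to both arms and cancels from group × time. This stands. A reader might infer that season biases the comparison of arms; under the Randomization section as written it does not. Chance imbalance in entry dates is not bias either, since the standard error already covers it. The reservation is the Study setting section, which puts the experimental arm at one institution and the control arm at another. That conflicts with stratification by centre, and it would remove the protection if the sites' calendars differed.

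**No seasonal pattern is documented.** This also stands. The Introduction's remark on sunshine concerns the behaviour of city dwellers, not the calendar. It is tempting to say that season will produce a spurious rise, but the size and even the sign depend on an assumed amplitude and peak. The separation of the sampling windows does not depend on them.

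**The windows separate fully only on one clock.** True. It would be too strong to say without qualification that every last sample falls in June to November.

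**Covariates belong in the SAP.** Agreed: the absence of a calendar covariate from a condensed article is not in itself an error. The point is that the article fixes within-arm change as evidence of effectiveness, and a covariate cannot cleanly repair that. Entry date is constant within a person and cannot separate season from visit.

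**Uncontrolled within-arm change is weak evidence anyway**, for example through regression to the mean after selecting on 25(OH)D below 20 ng/mL. This is correct, and it supports the same remedy.

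**Conclusion.** The concern holds for the within-arm 25(OH)D analyses under objectives 2 and 3. On the Methods clock, visit and season are confounded with no shared calendar month; on the Discussion's clock the confounding is smaller but remains. The season-only 6-month change lies between −1.27A and +1.27A (−1.13A to +1.13A on the later clock) and includes zero. These bounds assume uniform entry and an annual cosine. A and the peak date are not in the documents, and the rejection rates above also rest on assumed SDs.

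The concern does not extend to the between-arm contrast under concurrent randomisation within centre. It would do so only if arms are tied to sites that recruit on different calendars, a matter on which the Study setting and Randomization sections disagree.

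**What to change.** 1. In the objectives and the Data analysis section, state that the 25(OH)D effectiveness conclusion rests on the concurrent between-arm difference. State that within-arm 25(OH)D change is descriptive, because it cannot be separated from season.
2. In the between-arm 25(OH)D model, add entry date, for example as one sine and one cosine term, for precision and to guard against calendar imbalance. In a repeated-measures model these terms must interact with visit; with complete data, a main effect alone leaves the group × visit contrast unchanged. An arm × season term is optional and exploratory.
3. Reconcile the two follow-up clocks, and correct the impossible end year in "LBP patients attending outdoor clinics of both centers from 1st December 2022 to 30th May 2022 will be primarily screened by the outdoor team".
4. Reconcile the Study setting section, which gives each arm its own site, with the Randomization section, which stratifies by centre.

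**Cost.** Items 1 and 2 change wording and add one or two degrees of freedom for the 6-month change (one if entry date is linear, two for the sine and cosine pair). The documents do not say that entry dates are recorded, but visit forms and laboratory reports ordinarily carry them. The real price is weaker within-arm claims. If arms do prove to be tied to sites, the adjustment relies on overlapping entry dates and the assumed seasonal form, and it does not resolve the confounding of arm with site.
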